### Participant timeline {13}

Table 3 outlines the time schedule of enrolment, intervention implementation, and assessments for study participants.

**Table 3 Tab3:** Participant timeline for the IFPLAN project’s cluster randomized controlled trial

Intervention implementation (Planned start April 2023 with implementation lasting for at least 1 year)			
**Visit**	**Visit 1: Baseline survey**	**Visit 2: Process evaluation**	**Visit 3: Endline survey**
**Visit time point**	Prior to intervention implementation	During/post intervention implementation	After intervention implementation
**Visit conducted by**	OPM Nigeria Data collection team	OPM Nigeria Data collection team	OPM Nigeria Data collection team
**ENROLMENT:**			
Eligibility screen	X	X	X
Informed consent of respondent	X	X	X
Resident, Household listing of women 18–49 years	X		X
Women 18–49 years, Washington Group Questions	X		X
**ASSESSMENTS:**			
Women 18–49 years, Respondent’s Background	X		X
Women 18–49 years, Husband’s background	X		X
Women 18–49 years, Marriage and sexual activity	X		X
Women 18–49 years, Fertility preferences	X		X
Women 18–49 years, Reproductive history	X		X
Women 18–49 years, Knowledge of contraceptive methods	X		X
Women 18–49 years, Contraceptive use	X		X
Women 18–49 years with disabilities, Inclusion and participation	X		X
Women 18–49 years with disabilities, Attitudes	X		X
Women 18–49 years, HIV knowledge	X		X
Women 18–49 years, Experience of gender-based violence	X		X
Programme monitoring data on key intervention components		X	
Women 18–49 years, Participant response to family planning services		X	
Women 18–49 years, Unintended consequences of family planning services		X	
Women 18–49 years, Contextual factors affecting use of family planning services		X	
Health facility staff, intervention set-up and delivery		X	
Health facility staff, perceived impact and operation of the intervention		X	
Intervention implementers, intervention set-up and delivery		X	
Intervention implementers, perceived impact and operation of the intervention		X	

### Sample size {14}

Calculations were conducted in Microsoft Excel [31], based on Hayes & Bennett [32]. The assumptions, as summarized in Table 4, were used in determining the likely number of women 18–49 years with disabilities who will be living in the catchment areas of the healthcare facilities, as this is the target population for the evaluation. Various plausible estimates of the between-cluster coefficient of variation (*k*) and effect sizes were explored. Determination of the sample size was guided by the number of areas that the Sightsavers team has capacity and funding to reach, and security concerns limiting implementation to Kaduna city. Assuming *k* = 0.3, a 5% significance level, and 80% power, the trial will be able to detect a risk ratio of 1.5 (i.e. a 50% increase in access compared to the control arm) with 25 women with disabilities interviewed in each cluster. This design will require approximately 20,000 households to be screened for eligible women. It was originally intended to have 19 clusters per arm (a total of 38 clusters overall); however, it was only possible to identify a total of 37 clusters in Kaduna city, consequently 19 clusters were assigned to the intervention arm and 18 clusters to the control arm.

**Table 4 Tab4:** Assumed and derived values for the IFPLAN cluster randomized controlled trial sample size calculations

**Assumptions:**	
Proportion of women aged 18–49 years	20.0%
Proportion of women 18–49 years who are disabled based on Washington Group Questions^a^	0.7%
Proportion of women 18–49 years with depression or anxiety^b^	6.0%
Estimated overlap between the above	30%
Number of people in each cluster	10,000
Proportion of women who have ‘access’ to family planning	25%
**Derived values:**	
Number of women aged 18–49 years (10,000 × 20%)	2000
Proportion of women 18–49 years who are disabled overall (6% + (0.7% × (100–30%)))	6.49%
Number of women 18–49 years who are disabled (2000 × 6.49%)	130

^a^This is women who report ‘a lot of difficulty’ or ‘cannot do at all’ to one of the six domains in the Washington Group Short Set of questions [23], with this prevalence found in the DHS 2018 data for women 18 to 49 years old in Nigeria

^b^This is the proportion of women who report depression or anxiety using the questions from the Washington Group Enhanced set of questions [23]. This value is based on research in Lagos, in the south of Nigeria [9]

### Recruitment {15}

Health facilities that met the eligibility criteria were recruited to participate in the trial by Sightsavers. For recruitment of the women of reproductive age, female enumerators working for OPM Nigeria conducted a house-to-house survey to find women in the included age range of 18–49 years. Those identified as having a disability based on the Washington Group questions are asked to enroll in the study [23]. The participants are given the opportunity to opt to complete the full survey at a different, and more convenient, time. Loss of time by participants will be the main burden of their involvement in the evaluation. Due to the length of the baseline and endline surveys a non-monetary incentive, such as soap or detergent, will be given to participants.

A neighbourhood-matched sample of women without disabilities will also be interviewed for each woman with disabilities included in the sample; these will be recruited as the next woman of reproductive age within ± 5 years of age, without disabilities, who consents to take part in the study.

## Assignment of interventions: allocation

### Sequence generation {16a}

Cluster allocation was conducted through a random draw. The first 19 clusters drawn were allocated to the intervention arm and the remaining 18 clusters allocated to the control arm.

### Concealment mechanism {16b}

Cluster numbers were hidden during allocation using concealed cards.

### Implementation {16c}

Intervention assignment was conducted at one time point before the start of the trial during a multi-stakeholder event organized by Sightsavers for implementation of the IFPLAN project. The random draw was conducted by government officials in Kaduna during the event.

## Assignment of interventions: Blinding

### Who will be blinded {17a}

No blinding amongst participants, data collectors, or data analyst. Given the nature of the intervention, health facilities in clusters assigned to intervention or control will be aware of their allocation and women in the catchment area may also be aware of the health facility or their community’s allocation—making it impossible to maintain blinding of the data collectors. Given that there are also 19 clusters in the intervention arm and 18 clusters in the control arm, blinding of the data analyst will not be possible.

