### Outcomes {12}

The primary outcome for the trial, as shown in Table 2, is access to modern family-planning methods. We will also measure ‘realized access’, or *use*, as an important secondary outcome, defined as women aged 18–49 with disability who are sexually active and would like to delay or reduce future pregnancies and are using modern family-planning methods to achieve this.

**Table 2 Tab2:** Summary of outcomes for the IFPLAN project’s cluster randomized controlled trial

	**Outcome name**	**Measure**
**Primary outcome**	Access to family planning	Survey: binary (yes / no), based on composite of questions: • Know of at least three modern contraceptive methods that are available; & • Know where to access modern family-planning; & name the location; & list the available family planning services; & • Believe that they could use services if they needed them
**Secondary outcome**	Knowledge of family planning	Survey: binary (yes / no), based on composite of questions: • Know of at least three modern contraceptive methods that are available
	Intention to use	Survey: binary (yes / no), based on: • Will use contraceptive method in the future
	Use of family planning (modern method)	Survey: binary (yes / no), based on composite of questions: • Participant or participant’s partner currently doing something or using any method to delay or avoid getting pregnant; & • (Using a modern contraceptive method)
	Unmet need for family planning	Survey: binary (yes / no), based on composite of questions: • Would prefer to delay or not to have another child & • Not using contraception
	Perceived attitudes towards women with disabilities	• Score based on inclusion and participation module of survey

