## Data collection and management

### Plans for assessment and collection of outcomes {18a}

Data will be collected by experienced and trained female enumerators, overseen by OPM Nigeria. All data collection tools and procedures will be pre-tested and piloted prior to use.

The trial will collect baseline and endline data from all of the health facility catchment areas included in the study using household surveys. The baseline survey will be conducted prior to implementation of the project interventions and the endline survey will be conducted after at least 1 year of IFPLAN activity implementation.

Project monitoring data will be routinely collected by implementing partners to support intervention implementation and shared with LSHTM for the purposes of the process evaluation. During and/or after the IFPLAN project, semi-structured interviews will be undertaken with women of reproductive age with disabilities in the intervention arm to understand participant responses to the interventions, identify any unintended consequences, and compare their experiences to women without disabilities in the intervention arm, and women with disabilities in the control arm (approximately 30 interviews conducted in total). Furthermore, key health facility staff and intervention implementers will be interviewed to elucidate mechanisms of impact and contextual factors for implementation.

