### Methods in analysis to handle protocol non-adherence and any statistical methods to handle missing data {20c}

We will adopt an intention-to-treat analysis, and therefore health facility catchment areas will be analysed per their original arm assignment even if subsequently the intervention is not implemented in any or all of the health facilities in that cluster. Given that the health facility catchment areas are close together due to the small geographical area of Kaduna city, respondents will be asked about which facility they attend for family planning services and their participation in community-based family-planning activities in order to conduct a sensitivity analysis using an as-treated per-protocol analysis. Furthermore, should health facility staff be transferred between facilities from the intervention arm to control arm (or vice versa) this will be captured through the process evaluation and its potential effects explored.

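### The 19/18 cluster split does not rule out a masked analysis, and possible respondent awareness does not make all enumerator masking impossible

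*Protocol article*

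**What the plan says.** Who will be blinded {17a} opens with "No blinding amongst participants, data collectors, or data analyst". Two separate reasons follow.

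- **Data collectors.** Facilities will know their allocation, and "women in the catchment area may also be aware of the health facility" or community's allocation. The section describes this as "making it impossible to maintain blinding of the data collectors".
- **Analyst.** The only reason given is the unequal number of clusters: 19 intervention and "18 clusters in the control arm, blinding of the data analyst will not be possible".

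Other sections bear on this:

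- Table 2 (Outcomes {12}) defines the primary outcome as a binary survey composite. Its components include "Know of at least three modern contraceptive methods that are available", knowing and naming a location and listing its services, and "Believe that they could use services if they needed them".
- Plans for assessment and collection of outcomes {18a}: "Data will be collected by experienced and trained female enumerators, overseen by OPM Nigeria".
- Table 3 (Participant timeline {13}) repeats household listing, the Washington Group questions and the eligibility screen at endline.
- The section on non-adherence and missing data {20c} adds that "respondents will be asked about which facility they attend for family planning services and their participation in community-based family-planning activities", in support of an as-treated sensitivity analysis.
- Implementation {16c}: allocation was drawn before the start of the trial at a multi-stakeholder event.

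**The concern.** The section declares masking not possible for the analyst and impossible for the data collectors, on grounds that do not establish either. This is a stated rule with a faulty reason, so it cannot be put down to detail left for an analysis plan.

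Two kinds of bias are at stake. The first is differential recording. Whether a woman has named a third method, given an acceptable location or affirmed a belief depends partly on how the interviewer probes and codes. An interviewer who knows the arm may do this differently. The same applies to the endline screening questions that determine eligibility. The second is analyst discretion. Statistical methods {20a} refers to basic respondent and catchment-area characteristics and to variables that appear imbalanced, and {20c} to as-treated groups built from survey answers. Wherever these are finally specified, fixing them without sight of results by true arm protects the comparison.

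**Working it through.** **1. The plan's own figure.** Inputs from Sample size {14} and Table 4: control proportion 0.25, risk ratio 1.5 (so 0.375), k = 0.3, 25 women with disabilities per cluster, 5% significance (two-sided assumed) and 80% power. The Hayes and Bennett formula for unmatched clusters gives

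c = 1 + (1.96 + 0.84)² × [0.25×0.75/25 + 0.375×0.625/25 + 0.3²×(0.25² + 0.375²)] / 0.125²

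The bracket is 0.0075 + 0.009375 + 0.01828 = 0.03516. Divided by 0.015625 it is 2.25. With (1.96 + 0.84)² = 7.85 from unrounded z-values, c = 18.66, rounded up to 19. Then 19 × 25 = 475 per arm and 950 in total, as stated. With 19 and 18 clusters, power is about 80% with the one-cluster-per-arm correction and 82% without it. Masking does not enter this formula, so none of these figures changes.

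**2. Analyst.** Under plain A/B coding, anyone who knows the split can tell that the group of 19 is the intervention arm. To that extent the stated reason is true. If the arm variable is withheld, or replaced by a random 19/18 relabelling of the 37 clusters, the counts carry no information about the true arms. The reason therefore excludes one coding method and not masked analysis.

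**3. Enumerators.** The premise about women is that they may be aware. The conclusion is that masking is impossible. What follows from the premise is that some enumerators will learn the arm of some clusters. The article describes no measure to limit this.

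**4. How much of eligibility rests on mood items.** From Table 4: 0.7% functional difficulty, 6.0% depression or anxiety, 30% overlap, 6.49% overall.

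- Overlap: 0.7% × 30% = 0.21%.
- Depression or anxiety alone: (6.0 − 0.21)/6.49 = 5.79/6.49 = 89%.
- Depression or anxiety with or without functional difficulty: 6.0/6.49 = 92%.

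**5. Illustration only.** The bias sizes here are assumptions; the document gives none. Suppose there is no true effect, access is 25% in both arms, and a fraction of intervention-arm women without access is credited with it.

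- 5% credited: 0.25 + 0.05 × 0.75 = 0.2875, apparent risk ratio 1.15.
- 10% credited: 0.25 + 0.10 × 0.75 = 0.325, apparent risk ratio 1.30.

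With k = 0.3, 25 per cluster, 19 and 18 clusters less one per arm, and a normal approximation, the two-sided rejection rate under differential recording is:

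| Shift in intervention arm (points) | Rejection rate |
|---|---|
| 0 | 5% |
| 2 | 8% |
| 3 | 12% |
| 5 | 23% |
| 10 | 63% |

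A 5-point shift is 5/12.5 = 40% of the target difference. The table shows sensitivity to such a shift and does not say that a shift of any size will occur.

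**The case against.** The strongest reply is that enumerator masking would fail in practice. The draw took place at a multi-stakeholder event. The intervention is locally visible, with facility improvements, town hall meetings, community plays and household visits (Intervention description {11a}). Arm belongs to the cluster, where about 25 women with disabilities and 25 matched women are interviewed, so one disclosure unmasks an enumerator for her later interviews there. The primary outcome itself asks for a location and its services, so talk of facilities cannot all be moved to the end. The same organisation's data collection team carries out the surveys and the process evaluation (Table 3). Respondents are unmasked in any case. All of this stands, and it limits what can be gained to partial protection.

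A reader might infer that enumerators were left unmasked without thought, or that both groups could be largely masked at no cost. The document supports neither. It gives a reason for the enumerators, and separating survey staff from process-evaluation staff could carry a cost. Nor does it show that unmasked staff decide who enters: entry follows fixed response thresholds, and the matched woman is the next eligible one who consents. The risk lies in how answers are elicited and recorded.

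It is also fair to say that covariates and as-treated groups may be fixed in an analysis plan that is not shown, and that the exposure questions may already come last in the form. Their absence from the article is not the point. Enumerator training, piloted tools, programmed data checks and field supervision reduce recording error, but none is described as addressing knowledge of the arm. Finally, because the outcome is a conjunction, a false positive requires every failed component to be credited, so the risk ratios of 1.15 and 1.30 must not be read as estimates.

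**Conclusion.** The point holds in limited form. For the analyst, the stated reason is wrong as a general claim: the 19/18 split defeats plain A/B coding only, and locking the program on a withheld or permuted allocation is close to free. The final run will still be unmasked; what is protected is the set of choices made before it. For enumerators, possible awareness among women does not justify abandoning all masking when the primary outcome is interviewer-recorded knowledge and belief and screening is repeated at endline. The achievable gain is partial and leaves respondents' own reporting bias untouched.

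The size of any bias cannot be estimated from the document. The 89% (92% with overlap) shows how far eligibility depends on self-reported mood items under Table 4's assumptions. Functional items are self-reported too, so that share does not by itself isolate a masking problem. The trial is not invalidated, but the section should be amended.

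**What to change.** Amend Who will be blinded {17a} in two places.

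1. **Analyst.** Replace the sentence on the 19/18 split. State that the program for the primary and secondary analyses, including covariates and as-treated definitions, is written and locked on endline data with the allocation withheld or permuted (19/18). The facility-attendance and activity-participation answers are held back until then, since they could reveal the arms. The true allocation is merged only after the lock.
2. **Enumerators.** State that survey enumerators are not given the cluster allocation, that screening and outcome modules come before the facility-attendance and activity-participation questions, and that enumerators record whether and when they learned the arm. Report that record by arm.

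The cost is protocol wording, a person outside the analysis to hold the allocation, a check of question order on the tablet form and one added item. Keeping survey and process-evaluation staff apart may add some cost. Trial status anticipates the endline survey for 2024, so on this document's timeline the changes could be made before it. The amended text should say plainly that enumerator masking is partial and that respondents remain unmasked.

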### Procedure for unblinding if needed {17b}

Not applicable, as there is no blinding in the trial unblinding will not occur.

## Data collection and management

### Plans for assessment and collection of outcomes {18a}

Data will be collected by experienced and trained female enumerators, overseen by OPM Nigeria. All data collection tools and procedures will be pre-tested and piloted prior to use.

The trial will collect baseline and endline data from all of the health facility catchment areas included in the study using household surveys. The baseline survey will be conducted prior to implementation of the project interventions and the endline survey will be conducted after at least 1 year of IFPLAN activity implementation.

Project monitoring data will be routinely collected by implementing partners to support intervention implementation and shared with LSHTM for the purposes of the process evaluation. During and/or after the IFPLAN project, semi-structured interviews will be undertaken with women of reproductive age with disabilities in the intervention arm to understand participant responses to the interventions, identify any unintended consequences, and compare their experiences to women without disabilities in the intervention arm, and women with disabilities in the control arm (approximately 30 interviews conducted in total). Furthermore, key health facility staff and intervention implementers will be interviewed to elucidate mechanisms of impact and contextual factors for implementation.

### Plans to promote participant retention and complete follow-up {18b}

Adaptations will be put in place to support the direct participation of people with different impairments in data collection. For example, sign language interpretation or options to provide written responses will be made available to people with profound hearing impairments. Simplified information sheets will be used for people with cognitive or intellectual impairments in the process evaluation.

### Data management {19}

Data entry for the baseline and endline surveys will be conducted electronically using tablets, with digital forms programmed using SurveyCTO [33], replicating the paper forms approved by the Institutional Review Boards. Validation and consistency checks will be programmed into the data collection forms and applied at the point of data entry into a specific field. Collected data will be password protected on devices and servers.

For the process evaluation, interviews will be audio recorded, alongside written interview notes. Interviews will be recorded, transcribed, and translated into English as soon as possible after the interview. A sample of interview recordings from each interviewer will be checked to ensure that these were conducted in accordance with the topic guide and qualitative interview best practices. Anonymized project monitoring data shared with LSHTM will be reviewed and relevant data extracted by the study team for the purpose of the process evaluation.

### Confidentiality {27}

Field staff will sign a confidentiality agreement to not disclose any information outside of the study, unless for safeguarding purposes. Given that some of the questions in the survey relate to gender-based violence, if any women disclose that they have been a victim of gender-based violence or the enumerator suspects that they might be, the enumerators will confidentially refer the respondent to local organizations that support victims of gender-based violence and discreetly share a small information card with the organizations’ contact information. Paper consent forms with participant names will be stored separately to the survey data and stored in a locked cabinet. Collected data will be anonymized using unique identification numbers.

